# Study Methods

## Trial design

The phase 2b will be a double-blind, placebo-controlled randomized study to assess clinical benefit and safety of the phase 2a selected dose of XAV-19 in 398 hospitalized adults with COVID-19 associated moderate pneumonia.

The study is a multicenter trial that will be conducted in up to approximately 40 sites globally. The study will compare an investigational therapeutic agent to a control arm.

Patients will be randomized to either XAV-19 or placebo in a 1:1 ratio and will receive a single dose based on the analysis of the Phase 2a study. Randomization will be stratified by site and duration since onset of COVID symptoms (1 to 6 days, 7-10 days and 11-14 days).

An independent Data and Safety Monitoring Board (DSMB) will actively monitor interim data to make recommendations about early study closure.

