## Randomization

Enrollment and randomization of subjects is done online, using the eCRF, the day of the infusion or the day before.

Eligible subjects will be randomized and assigned in a 1:1 ratio to either Xav19+Soc or placebo+Soc, with stratification by site and by duration since onset of COVID symptoms (1-6 days, 7-10 days, 11-14 days).

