## Sample size calculation

In the phase 2b, about 398 randomized patients, 199 patients in each group, will be included.

Assuming a true treatment difference in clinical failure rate of 10% for XAV-19 added to SoC therapy compared to placebo added to SoC therapy where a rate of 20% is expected, a sample size of 398 participants provides at least 80% power that the primary analysis will be statistically significant at the two-sided 5% significance level.

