# General statistical considerations

## General Principes

### Confidence intervals and p-values

All applicable statistical tests will be 2-sided and will be performed using a 5% significance level.

No correction for multiple comparisons will be applied; all secondary objectives will be considered as exploratory and results were reported with only effect size estimates with their confidence intervals (CIs). All CIs presented will be 95%CI and 2-sided.

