### Primary and key secondary outcome analyses

Proportion of patients who die, develop respiratory failure (requiring noninvasive ventilation, high-flow oxygen devices or invasive mechanical ventilation) between Day 1 and Day 15 (Day 8 and Day 29) will be compared using a logistic mixed model to take into account stratification factors: duration of symptoms prior to screening (fixed effect) and center (random effect).

In cases of convergence failure, sensitivity analysis of the primary outcome will be performed to assess the impact of individual centers on the observed treatment effect. If centers effect is not relevant, final model will not include the center.

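### If the primary mixed model does not converge, SAP 5.2 ties the choice of final model to the observed treatment effect, gives no criterion, and names no model if center matters

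*Combined protocol and SAP*

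**What the plan says.** SAP 5.2, under the primary and key secondary outcome analyses, compares the arms with a logistic mixed model: symptom duration as a fixed effect, center as a random effect. When that model does not converge, the SAP calls for a sensitivity analysis of the primary outcome "to assess the impact of individual centers on the observed treatment effect". It then gives a single consequence: "If centers effect is not relevant, final model will not include the center". Nothing follows for the opposite case.

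Other sections bear on this but do not settle it:

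- Protocol 7.2.1 specifies a logistic mixed model with both stratification factors, gives no fallback, and leaves further detail to the SAP.
- Protocol 7.2.5 says only that no change to the analysis strategy is expected.
- SAP 2.6 places the primary analysis after unblinding.
- SAP 3.2 describes a blind review, but only of protocol deviations.
- SAP 3.1 names SAS 9.4 and allows other packages such as R. It states no procedure, estimation method or convergence criterion for the mixed model.

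On design, SAP 2.1 says: "The study is a multicenter trial that will be conducted in up to approximately 40 sites globally".

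**The concern.** A fallback for the deciding test should be fixed before anyone can see which option favours which conclusion. Here the step that decides whether center stays in the model is an examination of how centers move the treatment effect, and that examination needs the treatment allocation. With no threshold for relevance, two competent analysts could reach different final models from the same data, both within the SAP.

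The second gap is more basic. If the model has not converged and center is judged relevant, the SAP names no analysis at all, so the primary result would have to come from a model chosen at that moment. At stake is the standing of a borderline result in a trial planned at almost exactly 80% power.

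**Working it through.** **1. The plan's own figure.** Inputs from SAP 2.7 and 3.1: "placebo added to SoC therapy where a rate of 20% is expected", a 10-point reduction, two-sided 5%, 80% power, 1:1 allocation. With pooled variance and no continuity correction:

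n per arm = [1.960 × √(2 × 0.15 × 0.85) + 0.842 × √(0.20 × 0.80 + 0.10 × 0.90)]² / 0.10² = (0.990 + 0.421)² / 0.01 ≈ 199.

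The total is 398, as stated; power at 199 per arm is 0.8001. The sample size is not in question.

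**2. Is the branch plausible?** 398 / 40 ≈ 10 patients per center at the upper limit on sites. Expected events at the planned rates are 199 × 0.20 + 199 × 0.10 ≈ 60. In simulation, about 13 of 40 centers had no event at 20% versus 10%, and about 10 had none with both arms at 20%. Sparse centers are a common setting for fitting problems, so a fallback is worth having. This does not give a probability of convergence failure, and neither do the documents.

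**3. The decision paths as written.**

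| Mixed model | Center judged | Final model in SAP 5.2 |
|---|---|---|
| Converges | not asked | Mixed model |
| Fails | not relevant (undefined) | Logistic without center |
| Fails | relevant (undefined) | None named |

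**4. How much the choice matters.** Simulated trials had 398 patients in 40 centers of unequal size, blocks of 4 within center and duration stratum, a 30/50/20% duration split, and a between-center SD of 0 or 0.5 on the logit scale. The number of centers is the SAP's upper limit. The center sizes, block size, duration split and SDs are assumptions not found in the documents.

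*The two models SAP 5.2 names* (500 trials per setting):

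- Disagreement on significance: 0.2% and 0.8% under no effect (SD 0 and 0.5), and 0.4% at the planned effect. That is 1 to 4 trials in 500; the simulation standard error at 0.8% is √(0.008 × 0.992 / 500) ≈ 0.4 points.
- Power at the planned effect: 82.0–82.8% with random center, 81.6–82.4% without center.

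*Filling the unnamed branch freely.* Three candidates that an analyst might plausibly use once the mixed model has failed, under no effect with both arms at 20% (4,000 trials per setting):

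| Test | SD 0 | SD 0.5 |
|---|---|---|
| Logistic, duration only | 4.7% | 4.6% |
| Logistic, center fixed | 5.8% | 5.9% |
| Mantel-Haenszel by center | 4.8% | 4.5% |
| Any of the three significant | 6.3% | 6.7% |

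The standard error of the last row is about √(0.067 × 0.933 / 4000) ≈ 0.4 points. Part of the excess over 5% belongs to the fixed-center model itself, which rejects in 5.8–5.9% of trials without any selection. Including the mixed model, the four analyses were not unanimous in 2.6–3.8% of null trials and 6.0–6.4% of trials at the planned effect (500 per setting).

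**The case against.** The strongest reply is that this is a contingency inside a contingency. It operates only when the model fails to converge. The one replacement that the SAP names, the model without center, almost always gives the same answer as the intended model and holds its error rate. The SAP also does not say when the center assessment takes place, and center effect could be read as the between-center variance, which can be examined blind.

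The point about size stands and sets the weight given below. The alternative reading is weaker: the preceding sentence directs the assessment at the observed treatment effect, which cannot be seen without allocation, and SAP 2.6 puts the primary analysis after unblinding. The timing is therefore an inference, but a firm one. Nothing in the reply supplies a criterion or fills the missing branch.

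Two stronger readings are tempting and should be resisted:

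- A reader might infer that the fallback would be reached in most trials, because the center variance was estimated as essentially zero in about 61–62% of simulated trials when centers do not differ (14–19% at SD 0.5). The SAP's trigger is convergence failure, not a zero variance. At zero variance the mixed model reduces to the no-center model, so nothing turns on the choice.
- A reader might infer that type I error could reach about 10%, the simulated figure if refits omitting one of the five largest centers could also be selected. The SAP calls the center-impact work a sensitivity analysis, and its only stated consequence is whether center stays in the model. Nothing allows a refit on fewer centers to become the primary result.

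**Conclusion.** The gap is real and of low severity; closing it is a cheap improvement. In the convergence-failure branch the deciding test is not pre-specified: relevance has no criterion, the judgment is tied to the treatment effect, and if center is judged relevant there is no primary analysis.

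The choice between the two named models changes significance in about 0.2–0.8% of simulated trials. The 6–7% type I error is an upper limit over the three models tried. It is conditional on reaching the fallback and on always taking the most favourable result, and it rests on the assumed site sizes and variances. It is not an expected error rate for the trial, whose overall exposure is smaller by the unknown probability of convergence failure.

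**What to change.** Before unblinding, replace the fallback paragraph in SAP 5.2 with wording such as:

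> Convergence failure is defined by the stated software, estimation method and convergence criterion. If the mixed model fails to converge, the primary analysis is the logistic model with treatment and symptom-duration stratum, without center. This is decided by convergence status alone, without reference to the treatment estimate. A center variance estimated as zero is not a failure, since the model then reduces to the no-center model. Analyses of the impact of individual centers are sensitivity analyses and cannot replace the primary result.

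The sponsor fills in the software, method and criterion, so that failure is not itself a matter of settings chosen later. Apply the rule to the ITT, mITT and PP analyses. For consistency, apply it also to the Day 8 and Day 29 endpoints: they share the model, but the present fallback mentions only the primary outcome.

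The cost is one paragraph. The sample size stays at 398 and no trial procedure changes. The downside is slightly less precision if center is dropped although sites differ. With a between-center SD of 0.5, simulated power was 81.6% without center against 82.0% with it, a difference within simulation error.

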### Secondary outcomes analyses

### NEWS score

The median time to discharge or to a NEWS ≤ 2 will be summarized by treatment group.

Time to discharge or to a NEWS ≤ 2 will be compared between groups using Fine & Gray method to take into account competing risk (death).

The mean, standard deviation (SD), median, IQR, minimum, and maximum NEWS at baseline and each study visit will be presented by treatment arm as well as change from baseline.

Change in NEWS score at specific time points will be summarized by proportions (e.g., proportion who have a 1-, 2-, 3-, or 4-point improvement or 1-, 2-, 3-, 4-point worsening).

### 8-point ordinal scale over 29 days

The median time to respiratory failure (value of 5, 6, 7, or 8 on the clinical status 8-point ordinal scale) from baseline will be estimated with Kaplan-Meier method. Frailty model will be used to compare this time by treatment group. If death is a competiting risk (in the case where one death happens before the respiratory failure), a survival analysis with death as competiting risk will be used instead.

The median time to improvement to one category of 8-point ordinal scale from baseline will be summarized by treatment group.

Time to improvement to one category will be compared between groups using Fine & Gray method to take into account competing risk (death).

The proportion of subjects in each severity rating on an 8-point ordinal scale at baseline and at Day 8, Day 15 and Day 29 will be presented by treatment group.

The number and proportion of subjects in each severity rating on an 8-point ordinal scale at Day 15 will be presented. The outcome will be analyzed using an ordinal regression model by treatment group.

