### Respiratory failure or death

Respiratory failure is defined by a requirement of low oxygen delivery device and a flow ≥ 10 L / min with reservoir, or high-flow oxygen devices or noninvasive ventilation, or invasive mechanical ventilation or death after infusion of treatment. This is related to a value of 5, 6, 7, or 8 on the clinical status 8-point ordinal scale.

Respiratory failure will be evaluated between baseline and day 15 (primary objective), between baseline and day 8, and between baseline and day 29 (key secondary objectives).

The primary outcome measures the number of patients who had at least one respiratory failure after baseline (D1 before infusion).

The time to respiratory failure will be defined as the elapsed time (in days) from baseline (on Day 1) to the first day at which a subject reaches any respiratory failure.

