### Primary and key secondary outcome

Subjects who withdrew their consent before Day 15 will be imputed using multiple imputation.

Subjects who are discharged but are subsequently re-admitted prior to Day 15 without a reported 8-point ordinal scale, their ordinal score will be imputed at 7, which is the highest value for a hospitalized subject.

For subjects who are discharged, if no visit is done at day 15 +/ 2 days then the reported ordinal score will be imputed at 2 (highest level for ambulatory patients).

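### Time to respiratory failure counts death as an event, but a single death before failure switches the analysis to one in which death is a competing risk

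*Combined protocol and SAP*

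**What the plan says.** SAP 5.1, *Respiratory failure or death*, lists the qualifying forms of respiratory support, including low-flow oxygen at 10 L/min or more with a reservoir, and closes the list with "or invasive mechanical ventilation or death after infusion of treatment". It adds: "This is related to a value of 5, 6, 7, or 8 on the clinical status 8-point ordinal scale". Time to respiratory failure runs from baseline "to the first day at which a subject reaches any respiratory failure".

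SAP 5.2, *8-point ordinal scale over 29 days*, takes up the same outcome: "The median time to respiratory failure (value of 5, 6, 7, or 8 on the clinical status 8-point ordinal scale) from baseline" is to be estimated by Kaplan-Meier, and the arms are to be compared with a frailty model. The next sentence gives the exception, for the situation in which death is a competing risk: "in the case where one death happens before the respiratory failure), a survival analysis with death as competiting risk will be used instead". It does not restate the event for that case and does not name the competing-risk model.

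The figure showing the scale is not reproduced, but the text fixes what score 8 is. SAP 5.4 says of patients readmitted without a score that "their ordinal score will be imputed at 7, which is the highest value for a hospitalized subject", and SAP 5.1 (*Days of Ventilation/ECMO*) assigns ventilation and ECMO to 6 or 7. That leaves 8 for death.

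**The concern.** An outcome cannot be both the event of interest and a competing event in the same analysis. Under the definition in 5.1, repeated by score in 5.2, a patient who dies without earlier respiratory support has reached the event on the day of death, and no death can come before it. The exception has content only if death is first taken out of the event, which the SAP does not say.

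Two statisticians could therefore program this paragraph differently. One would find that the condition is never met and keep the composite. The other would find one death without prior failure, recode it as competing and report non-fatal failure. The second result would no longer correspond to the primary and key secondary composite, and which quantity is estimated would have been settled by whether a single such death occurred anywhere in the trial.

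**Working it through.** **1. The texts side by side.**

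| Place | Is death part of the event? |
|---|---|
| SAP 5.1, *Respiratory failure or death* | Yes, named and linked to scores 5 to 8 |
| SAP 5.2, event for time to respiratory failure | Yes, through score 8 |
| SAP 5.2, exception in the same paragraph | No: death competes with the event |
| SAP 1.3 and 5.2, primary and key secondary composite | Yes |

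No other section resolves the third row. If death stays in the event, the exception is void. If the exception operates, deaths without prior failure leave the event. A patient who fails and later dies is unaffected, because the event is dated at the failure.

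The score-only wording in 5.2 adds an ambiguity. SAP 1.3 lists the reservoir criterion beside a score of 5 or more, and SAP 5.1 ties score 5 to non-invasive ventilation or high-flow oxygen. Once death is taken out, a patient who dies after only a reservoir mask at 10 L/min or more could be read from scores as dying before failure, although 5.1 already counts that patient as failed.

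**2. The plan's own figure (SAP 2.7).** Inputs: 20% vs 10%, two-sided 5%, power 80%.

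n per arm = [1.960 × √(2 × 0.15 × 0.85) + 0.842 × √(0.20 × 0.80 + 0.10 × 0.90)]² / 0.10² = (0.990 + 0.421)² / 0.01 ≈ 199, so 398 in total, with power 80.0%. The stated size reproduces. No design figure is given for time to respiratory failure.

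**3. Chance that the exception is triggered.** The documents give no risk *r* of death without prior failure, so *r* is an assumption. P(at least one) = 1 − (1 − r)^398.

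| Assumed r | P(at least one) | Expected number, 398 × r |
|---|---|---|
| 0.1% | 33% | 0.4 |
| 0.25% | 63% | 1.0 |
| 0.5% | 86% | 2.0 |
| 1% | 98% | 4.0 |

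**4. Size of the recoding.** Planned events by Day 15 = 199 × 0.20 + 199 × 0.10 = 59.7, about 60. At r = 0.5% and 1%, 2.0/59.7 = 3% and 4.0/59.7 = 7% of these would be recoded.

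For illustration, the planning rates imply a hazard ratio of ln 0.90 / ln 0.80 = 0.47. Schoenfeld power is Φ(|ln HR| × √d / 2 − 1.96). With d = 59.7 it is 0.83. With 5% of events recoded (d = 56.7) it is 0.81, and with 10% (d = 53.7) it is 0.79, holding the hazard ratio fixed.

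**5. The median.** A Kaplan-Meier median needs the event probability to reach 50%, which is 2.5 times the 20% assumed for control at Day 15. The outcome runs to Day 29, for which no rate is given, so the median is unlikely to be reached but this is not certain.

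**The case against.** The strongest reply is that little depends on this. SAP 3.1 makes every secondary objective exploratory, reported as estimates with confidence intervals. The primary and key secondary analyses keep death in the composite, and SAP 5.2 (*Death*) reports mortality at Days 15, 29 and 60 with Kaplan-Meier curves, log-rank test and Cox model, so an excess of deaths in one arm would be visible. The switch is also written in advance and depends on whether such a death occurs, not on the treatment comparison. All of this stands and limits the weight of the point.

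A reader might draw four stronger conclusions that the documents do not support:

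- *Deaths are removed from the endpoint.* Only deaths with no earlier failure could leave it, and even that is a consequence of the method, not a statement in the SAP.
- *The switch is almost certain to apply.* That holds at an assumed risk near 1%. At 0.1% the chance is 33%, and the documents give no rate.
- *The result could favour the arm with more deaths.* This can be constructed: with 30 vs 30 composite events (control vs XAV-19), of which 3 vs 9 are deaths without prior failure, the composite ratio is 1.00 and the non-fatal ratio is 21/27 = 0.78. But the example is invented and needs 12 such deaths, 3% of 398, split unevenly. Nothing in the plan suggests that pattern.
- *No median will exist.* The 10-20% rates are for Day 15 and the outcome runs to Day 29.

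It can also be said that failure without death, with death competing throughout, is a legitimate choice, since the SAP uses Fine & Gray for most of its other time-to-event outcomes. So it is, provided that it is fixed in advance and death is taken out of the event definition. It is not what SAP 5.1 defines.

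**Conclusion.** The contradiction is real and rests on the text alone: the exception in SAP 5.2 conflicts with the event in its own paragraph and with SAP 5.1. As written, it is either void or silently changes the estimand to non-fatal failure, depending on whether one death without prior failure occurs.

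The numerical effect is probably modest: at assumed risks of 0.5-1%, about 2-4 recoded patients against roughly 60 planned events. That comparison uses Day 15 planning rates and an assumed risk of death without prior failure. The sample size, primary test, key secondary analyses and mortality analyses are unaffected. The correction is still worth making, because the paragraph cannot be programmed in a single way.

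**What to change.** In SAP 5.2, *8-point ordinal scale over 29 days*:

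1. Delete the sentence that switches to a competing-risk analysis.
2. Define the outcome as time to respiratory failure or death by cross-reference to the full SAP 5.1 definition, including the reservoir mask at 10 L/min or more, and not by score alone.
3. Use Kaplan-Meier and the frailty model throughout.
4. Report cumulative incidence of failure or death with 95% CI at Days 8, 15 and 29 in addition to the median.
5. If non-fatal failure is also of interest, prespecify it as a separate, labelled analysis with death as the competing event. Name the model and show the result beside the cumulative incidence of death.

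The cost is a few sentences in the SAP and slightly simpler programming. No new data are needed and the sample size does not change.

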Proportion of patients who die, develop respiratory failure (requiring non-invasive ventilation, high-flow oxygen devices or invasive mechanical ventilation) between baseline and Day 15 will be compared using a logistic mixed model to take into account stratification factors (duration of symptoms prior to enrolment and sites).

Secondary hypotheses have been ordered according to relative importance.

The key secondary outcome, which is the proportion of patients who die, develop respiratory failure (requiring non-invasive ventilation, high-flow oxygen devices or invasive mechanical ventilation) between baseline and Day 8 and Day29 will be analysed as the primary endpoint.

Others secondary endpoint :

Quantitative endpoint will be compared using linear mixed model and qualitative data with logistic mixed model to take into account stratification factors.

Time data’s will be analyzed using survival model (Kaplan-Meier, Cox model). Fine & Gray method will be used to take into account competing risk.

Safety Analyses

The safety population is defined as all subjects randomized into the study but excluded who are ineligible at baseline or who have not had any dose of treatment.

Safety endpoints include death through Day 29 and through Day 60, SAEs and Grade 3 and 4 AEs. These events will be analyzed univariately. Time-to-event methods will be used for death. Each AE will be counted once for a given subject and graded by severity and relationship to COVID-19 or study intervention. AEs will be coded using the current version of the Medical Dictionary for Regulatory Activities (MedDRA). AEs will be presented by system organ class, duration (in days), start- and stop-date. Adverse events leading to premature discontinuation from the study intervention and serious treatment-emergent AEs will be presented either in a table or a listing.

More details will be described in the Statistical Analysis Plan.

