### Death

Mortality rate will be summarized by treatment group at day 15, day 29 and day 60.

Time data’s will be analyzed using a stratified log-rank test by treatment groups. Differences will be summarized with Kaplan-Meier curves and 95% confidence bounds.

The median time to event and 95% CI in each treatment group will be summarized and log rank test will be performed. Differences in time-to-event endpoints by treatment arm will be summarized with Kaplan-Meier curves. Number at risk, hazard ratio and log rank p-values will be presented on the figures.

Hazard ratio and 95%CI will be performed using Cox proportional hazards model.

28-day mortality may be summarized according to proportions by category and/or odds ratios with confidence intervals.

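### The SAP does not name the stratification factors in the Day 15 ordinal analysis and leaves the log-rank test for death undefined

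*Combined protocol and SAP*

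**What the plan says.** Randomisation is 1:1, stratified by site and by symptom duration of 1–6, 7–10 or 11–14 days (protocol 7.2.7; SAP 2.4). SAP 2.1 expects up to about 40 sites.

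For the other secondary endpoints, protocol 7.2.1 states: "Quantitative endpoint will be compared using linear mixed model and qualitative data with logistic mixed model to take into account stratification factors". Its next sentences, on time-to-event data, name Kaplan-Meier, Cox and Fine & Gray and mention no stratification factor.

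In SAP 5.2:

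- The primary and key secondary model is a logistic mixed model with symptom duration as a fixed effect and center as a random effect, and it has a fallback if convergence fails.
- For the 8-point scale at Day 15 the text reads: "The outcome will be analyzed using an ordinal regression model by treatment group". No covariate is named or ruled out.
- For death, time data are to be "analyzed using a stratified log-rank test by treatment groups", with no strata named. The next paragraph says: "The median time to event and 95% CI in each treatment group will be summarized and log rank test will be performed". Log-rank p-values and a hazard ratio then go on the figures, and the hazard ratio comes from a Cox model with no strata or covariates stated.

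SAP 3.1 treats all secondary objectives as exploratory, to be reported as effect sizes with confidence intervals only. It also says: "All applicable statistical tests will be 2-sided and will be performed using a 5% significance level".

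**The concern.** An analysis should normally carry the factors by which patients were randomised. The protocol commits to this for qualitative secondary endpoints, and the SAP does it explicitly for the primary and key secondary endpoints. A programmer who reads the ordinal sentence next to that model would probably fit treatment alone. Balancing the arms on prognostic strata and then ignoring those strata gives a test that rejects too rarely. In a proportional-odds model it also gives an odds ratio closer to 1 than the within-stratum effect. That matters because the SAP reports these endpoints through their effect sizes.

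For death, the text does not tell the analyst which test to run, which strata to use, or whether the Cox model should match. The timing makes this worth closing. Under protocol 4.3.3 and SAP 2.6, the statisticians, the principal investigator and the scientific coordinator see unblinded data to Day 29 before the Day 60 data are final, yet mortality runs to Day 60. A choice left open until then would be made by people who know the allocation.

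**Working it through.** **1. The plan's own figure.** The only power statement is for the primary endpoint: "a sample size of 398 participants provides at least 80% power", with "placebo added to SoC therapy where a rate of 20% is expected" and a 10-point absolute difference. With pooled variance and no continuity correction:

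n per arm = [1.96·√(2·0.15·0.85) + 0.8416·√(0.20·0.80 + 0.10·0.90)]² / 0.10² = (0.990 + 0.421)² / 0.01 ≈ 199, or 398 in total, with power 0.8001.

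The figure is reproduced. Nothing below changes it. No power is stated for the ordinal or death analyses.

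**2. Ordinal scale: assumptions.** The documents do not give the category rates, the prognostic strength of the strata or the block size. The following are assumed:

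- control distribution over the eight categories of 35/25/8/14/6/2/4/6%
- 398 patients, 40 centers, and duration bands holding 25/50/25% of patients
- permuted blocks of 4 within center × duration
- duration effects of +g, 0 and −g on the log-odds scale, and a normal center effect with standard deviation s
- a true conditional odds ratio of 0.55 (log −0.60), or 1 for the null

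The odds ratio between the extreme duration bands is exp(2g): 1.8, 4.1 and 11.0 for g = 0.3, 0.7 and 1.2. Each setting has 700 simulated trials.

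**3. Ordinal scale: results.** T is the treatment-only model; T+D adds duration.

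| Strata (s, g) | Null rejection, T | Null rejection, T+D | Mean log-OR, T | Mean log-OR, T+D | Model SE, T | Model SE, T+D | Power, T | Power, T+D |
|---|---|---|---|---|---|---|---|---|
| None (0, 0) | 5.3% | 5.4% | −0.610 | −0.612 | 0.1848 | 0.1851 | 91.7% | 91.6% |
| Weak (0.3, 0.3) | 4.3% | 4.4% | −0.586 | −0.594 | 0.1847 | 0.1853 | 90.4% | 91.0% |
| Moderate (0.5, 0.7) | 3.9% | 5.0% | −0.544 | −0.573 | 0.1844 | 0.1866 | 85.1% | 87.7% |
| Strong (0.8, 1.2) | 3.6% | 4.4% | −0.484 | −0.544 | 0.1842 | 0.1892 | 78.3% | 83.9% |

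- Power gained by adjusting for duration is −0.1, 0.6, 2.6 and 5.6 points.
- The treatment-only odds ratio moves from a true 0.55 to exp(−0.586) = 0.56, exp(−0.544) = 0.58 and exp(−0.484) = 0.62.
- For the treatment-only model, the ratio of model SE to actual sampling SE is 0.98–0.99 with no prognostic effect, about 1.04 weak, 1.02–1.05 moderate and 1.10–1.18 strong.
- Monte Carlo error is about 3% on these ratios and √(0.05·0.95/700) ≈ 0.8 points on the null rejection rates.

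A separate simulation with 4,000 trials per setting and a log-odds effect of −0.5 agrees. With duration effects of ±0.8 and center SD 0.5, the treatment-only test had size 4.1% and power 66%, against 69% with duration. At ±1.0 the figures were 3.9%, 65% and 70%. At ±0.5 with center SD 0.3 the gain was about 1 point.

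**4. Death.** The strata are unnamed, so two candidates were compared with the unstratified log-rank test. The settings were 600 trials each, Day 60 control mortality set at 10% or 15%, and a hazard ratio of 1 or 0.5, all assumed.

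- Stratified by duration only: the two tests fell on different sides of 0.05 in 0.5–3.7% of trials, with almost no loss of information (for example, log-rank variance 11.23 against 11.25).
- Stratified by center × duration: they disagreed in 2–15% of trials. This gives up to 40 × 3 = 120 cells, or 398/120 ≈ 3.3 patients per cell. The variance fell, for example, from 11.25 to 9.76 (13% lost) and from 12.43 to 10.59 (15% lost).

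The choice of strata therefore matters more than whether the test is stratified by duration.

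**The case against.** The strongest reply is that all this is read from silence. The SAP also uses the phrase about treatment groups in its stratified log-rank sentence, so the phrase can coexist with stratification. Nothing in the SAP withdraws the protocol's commitment, and the later log-rank mentions under Death may be shorthand for the stratified test. This stands to the extent that the defect is under-specification. A reader might infer that the sponsor decided to drop the factors or chose an unstratified hazard ratio; the documents do not show that. But the SAP spells out both factors where it clearly uses them, so the text still needs completing.

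A reader might also infer that the Fine & Gray and Cox comparisons contradict the protocol. They do not: the protocol's time-to-event sentences name no stratification factor. The same SAP section also plans a frailty model for time to respiratory failure, though without naming the cluster.

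Finally, the endpoints are exploratory, so picking the more favourable of two mortality tests could not support a confirmatory claim. That also stands, and it limits the weight of the point. The log-rank p-values planned for the figures do, however, sit awkwardly with SAP 3.1's effect-size-only reporting.

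**Conclusion.** The point holds as an incomplete specification that differs from the protocol on the ordinal endpoint and leaves the death analysis open. Run as written, the Day 15 ordinal analysis is conservative and its odds ratio is nearer to 1 than the within-stratum effect, to the extent that the strata are prognostic. Adjusting for duration is worth about 0 to 6 points of power under the assumed strengths. The upper end needs an odds ratio of about 11 between the extreme duration bands. The model with a center random effect was not simulated.

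It is tempting to say that the unadjusted standard errors are too wide. That is not a general fact: the excess over the true sampling error is small unless the strata are strongly prognostic, and adjustment slightly raises the reported standard error (0.1866 against 0.1844 in the moderate setting). Nor should the 13–15% information loss for death be read as a property of the plan, because it applies only if the strata are center × duration, which the SAP does not say.

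Type I error is not inflated in the ordinal analysis. The Day 8 and Day 29 key secondary endpoints already carry both factors. The primary analysis and N = 398 are unaffected.

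**What to change.** In SAP 5.2, 8-point ordinal scale over 29 days: specify a proportional-odds model for Day 15 with treatment and symptom duration as fixed effects and center as a random effect, using the convergence fallback already written for the primary model.

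In SAP 5.2, Death: name one log-rank test, stratified by the three symptom-duration bands; fit the Cox model with the same strata; and delete the unqualified log-rank test. Avoid center × duration strata, which could give up to about 120 sparse cells. State whether the remaining p-value is shown, given the reporting rule in SAP 3.1.

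Adding duration to the Fine & Gray models is optional.

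The cost is a few sentences and a few lines of code. Both factors are recorded for randomisation, and no extra patients are needed. The wording should be settled before the Day 29 unblinding.
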